(3) MoCA (Montreal Cognitive Assessment): In traditional Chinese medicine, “Spirit” refers to the sum of vital activities and mental processes, including cognition, perception, and emotion. Cognitive function is therefore considered part of “Spirit” and reflects its regulatory capacity, which also influences cerebral function (30). Patients with PSD frequently present with concomitant cognitive impairment (31). The MoCA serves as a widely adopted tool for cognitive evaluation with strong reliability and validity (32). It assesses eight domains: attention, orientation, fluency, naming, visuospatial skills, abstraction, delayed recall, and sentence repetition. The total score is 30, with one additional point added for individuals with fewer than 12 years of education. A lower score indicates greater cognitive impairment. It will be used to quantify changes in cognitive function attributable to acupuncture.

(4) SWAL-QOL (Swallowing Quality-of-Life Questionnaire): The SWAL-QOL comprises 44 items covering appetite, mealtime duration, food selection, sleep, and psychological status, and is specifically developed to measure the quality of life of individuals with PSD (33). A higher score corresponds to better quality of life. It will be employed to evaluate the impact of acupuncture on patients' quality of life.

Assessment schedule: baseline (week 0), weeks 2 and 4, and week 6 (end-of-treatment). All assessments will be performed by trained, blinded evaluators.

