Statistical Modeling: For clinical outcomes and imaging metrics, linear mixed-effects models will be employed to assess within-subject change (baseline vs. week 6) and between-group differences (acupuncture vs. control), while adjusting for sex, age, stroke severity, and lesion volume (48). Correlation analyses will test associations between rs-fMRI/DTI metrics and clinical improvement in swallowing function (SSA/VFSS-based measures/MoCA/SWAL-QOL scales) (49, 50). This will aid in assessing whether alterations in brain networks correlate with improvements in swallowing function, thereby enhancing the clinical interpretability of imaging findings. Depending on the assumptions of normality and linearity, analyses will use either Pearson's correlation coefficient or Spearman's rank correlation coefficient.

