#### Clinical data analysis

2.11.2

All randomized participants will be included in the preliminary analysis according to the intention-to-treat (ITT) principle. Data will be analyzed with SPSS v25.0 (IBM, Armonk, NY, USA). A two-tailed *p*-value of ≤ 0.05 will be taken to indicate statistical significance, and continuous data will be reported as mean ± standard deviation (SD). For normally distributed continuous variables, an independent-samples *t*-test will be used, whereas for non-normally distributed data, the Mann–Whitney *U* test will be applied. Categorical and ordinal variables will be expressed as percentages (%) and analyzed using the chi-square test when expected cell counts are adequate (typically all expected counts ≥5), or Fisher's exact test when expected counts are small. Ordinal data will be analyzed using the rank-sum test.

The incidence of adverse events will be summarized in the safety analysis and compared between groups using the chi-square test or Fisher's exact test, as appropriate. Missing data for participants who withdraw or deviate from the protocol will be handled using listwise deletion or multiple imputation methods.

fMRI data will be analyzed by experienced imaging specialists. All statistical analyses will be performed by independent data analysts who are blinded to group allocation, thereby minimizing potential bias.

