**Figure 3 F3:**
[figure not shown]
SPIRIT schedule of enrolment, interventions, and assessments. EOT, End of Treatment; rs-fMRI/DTI at baseline (t0), and Week 6; SSA at t0/Weeks 2/4/6; VFSS/MoCA/SWAL-QOL at t0 and Week 6; AEs monitored throughout.

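### Clinical outcomes are assigned both to an adjusted mixed model and to unadjusted two-sample tests, and ordinal scales to both chi-square and rank-sum, with no analysis named as decisive

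*Protocol article*

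**What the plan says.** Two sections of the protocol article prescribe an analysis for the clinical outcomes.

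- Section 2.11.1, under Statistical Modeling: "For clinical outcomes and imaging metrics, linear mixed-effects models will be employed to assess within-subject change (baseline vs. week 6) and between-group differences", "while adjusting for sex, age, stroke severity, and lesion volume".
- Section 2.11.2, Clinical data analysis: "For normally distributed continuous variables, an independent-samples *t*-test will be used", with Mann-Whitney for non-normal data. No covariates are mentioned. The tests are not limited to baseline tables, and they are not called supportive.

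Section 2.11.2 also gives two rules for ordinal data. The first is "Categorical and ordinal variables will be expressed as percentages (%) and analyzed using the chi-square test", with Fisher's exact test when expected counts are small. The next sentence is "Ordinal data will be analyzed using the rank-sum test".

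Section 2.7.3 describes PAS as an 8-point ordinal scale and MBSImP as a set of ordinal component ratings that form a profile. Its heading defines all the secondary outcomes as mean changes in score.

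**The concern.** A statistician working from this text has two rules for SSA, MoCA and SWAL-QOL and three for PAS and MBSImP ratings (linear mixed model, chi-square or Fisher, rank-sum). No sentence ranks them. This is a conflict between rules the article states, not detail left for a later analysis plan: any plan built on it would have to overrule one section.

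At stake is which p-value stands for each clinical outcome. Clinical efficacy is a stated aim (section 2.1), and the Conclusions expect the results to serve as a reference for management guidelines. Blinding of the analysts lowers the risk of choosing by result, but it does not say which result counts.

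**Working it through.** **Sample size used.** Section 2.9 gives 20 per group, 40 in total, and 40 × 1.15 = 46 to randomise. This reproduces and is not disputed. The checks below use 20 per arm and two-sided 0.05. The article gives no effect size, SD or correlation, so those are assumptions: SD 1 at each visit, effect 0.6 SD, and baseline to week-6 correlation r of 0.3 to 0.7.

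**1. Mixed model against t-test on change.** Let D be the week-6 score minus the baseline score. With two visits, complete data, a random intercept and covariates as main effects only, the covariates cancel from D. The group-by-time contrast is then mean D (active) − mean D (sham), with standard error s_D × √(2/n) and 2 × 20 − 2 = 38 df. That is the t-test on change. A simulation of 150 trials (r = 0.5, effect 0.6 SD, four prognostic covariates) agreed: the statistics differed by at most 0.006 and significance never differed.

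**2. T-test on week-6 scores.** Section 2.11.2 does not say which score is tested. With unit SDs, the correlation between the week-6 and change statistics is (1 − r)/√(2(1 − r)) = √((1 − r)/2). Simulated power at 0.6 SD, 3000 trials per row:

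| r | correlation of the two statistics | power, t-test on week 6 | power, t-test on change |
|---|---|---|---|
| 0.3 | √0.35 = 0.59 | 45.0% | 34.9% |
| 0.5 | √0.25 = 0.50 | 45.3% | 43.8% |
| 0.7 | √0.15 = 0.39 | 46.5% | 67.3% |

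By step 1 the last column also stands for the mixed-model contrast. Even where power is nearly equal (r = 0.5), the statistics correlate at only 0.50, so the same trial can be significant on one and not on the other.

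**3. Other routes to disagreement.** Mann-Whitney, triggered by the observed distribution, tests a different quantity from the mixed model. Missing data also break the identity in step 1: a mixed model can keep a participant seen only at baseline, whereas a t-test on change cannot without imputation. Section 2.9 expects 15% dropout, and 46 × 0.15 = 6.9, so about 7 participants could be affected.

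**4. Ordinal rules.** In a two-arm table with 20 per arm, each expected count is half its column total. For all to reach 5, every occupied level needs at least 10 patients, so 40 patients allow at most four occupied levels. An 8-level PAS with more levels in use goes to Fisher under the section's own rule, and every one of the simulated tables did have an expected count below 5. Fisher ignores category order, as chi-square does.

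Simulated power, 4000 trials per row, with assumed reference-arm proportions of 25%, 15% and then six levels of 10%:

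| latent shift | chi-square | rank-sum | disagree on significance |
|---|---|---|---|
| 0 | 2.6% | 4.4% | 6.0% |
| 0.6 SD | 14.1% | 40.3% | 30.4% |
| 0.8 SD | 25.4% | 62.3% | 39.0% |

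The power ratios are 14.1/40.3 = 0.35 and 25.4/62.3 = 0.41. Part of the gap reflects the conservatism of chi-square in sparse tables (2.6% at no effect). Fisher's power was not simulated.

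**The case against.** The strongest reply is that the two routes are closer than they look. Section 2.7.3 defines the outcomes as changes, and with complete data the mixed-model contrast then equals the t-test on change. This stands. A reader might infer that every clinical outcome can give a different p-value under each section; the documents do not support that.

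Other stronger readings also fail:

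- **That the model omits the group difference in change, or tests a group effect averaged over both visits.** Section 2.11.1 names within-subject change and between-group differences, and the outcomes are defined as changes. An article may leave the explicit interaction term to the analysis plan, and nobody proposes the averaged effect.
- **That the conflict inflates the false-positive rate to about 11%.** That simulated figure assumes a regression with baseline as a covariate, which neither section specifies, and an analyst free to report any of three tests.
- **That the interim SSA data are lost.** Naming a baseline to week-6 comparison does not bar weeks 2 and 4 from the model, and a week-6 endpoint is legitimate.
- **That the visit schedule is contradictory.** Section 2.7.3 lists visits generally ("Assessment schedule: baseline (week 0), weeks 2 and 4, and week 6 (end-of-treatment"), while the Figure 3 legend itemises them by measure ("SSA at t0/Weeks 2/4/6; VFSS/MoCA/SWAL-QOL at t0 and Week 6"). The specific listing largely settles the general one.

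It is also fair to say that the outcomes are secondary and that section 2.9 calls the trial exploratory. That lowers the severity. It does not answer the missing ranking or the double rule for ordinal data, which no reading of the text reconciles.

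**Conclusion.** The point holds in two parts. First, continuous clinical outcomes have two prescribed analyses and neither is named as decisive. They can disagree when the two-sample test uses week-6 scores, when Mann-Whitney is triggered or when data are missing. Second, PAS and MBSImP ratings fall under two ordinal rules and a linear model. Under the assumed 8-level distribution at 20 per arm, chi-square has well under half the power of rank-sum at shifts of 0.6 and 0.8 SD.

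The sizes rest on assumed effects, correlations and a PAS distribution that the article does not give. They show that the choice matters, not by how much in this trial. This should be fixed; it is not critical, because the affected outcomes are secondary and the tests in section 2.11.2 do not bear on the imaging primary outcomes.

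**What to change.** Before unblinding:

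1. Name the mixed model of section 2.11.1, with the group difference in change from baseline to week 6 as the estimate, as the decisive analysis for SSA, MoCA and SWAL-QOL.
2. In section 2.11.2, restrict the t-test and Mann-Whitney to baseline description or sensitivity analysis.
3. Strike the word 'ordinal' from the chi-square/Fisher sentence, leaving those tests for nominal variables and adverse events.
4. Name one order-respecting method for PAS and MBSImP ratings (the rank-sum test already in the text, or proportional odds) and exempt them from the linear model. The method should work on the component ratings, since section 2.7.3 defines no MBSImP total.

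The cost is wording only, with no new data or visits. Section 2.15 reports that at manuscript submission the data were blinded and no primary outcome analyses had been done. If unblinding has since taken place, the date of the choice should be reported with the results.

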### Eligibility criteria

2.3

**Inclusion criteria:** (1) ischemic stroke and dysphagia diagnosed per accepted criteria (15, 16), with Kubota Water Swallowing Test (WST) ≥grade II; (2) aged 30–80 years; (3) stroke onset 2 weeks to 6 months prior; (4) conscious, hemodynamically stable, and able to comply with procedures; (5) written informed consent.

**Exclusion criteria:** (1) coma, Parkinson's disease, or Alzheimer's disease (AD); (2) Severe cardiac, renal, or other organ failure, or critically ill stroke with unstable vital signs. (3) failure to meet the diagnostic criteria for PSD or absence of cerebrovascular disease on neuroimaging; (4) inability to cooperate with evaluation or treatment, or poor adherence; (5) severe psychiatric disorders precluding cooperation with observation or treatment; and (6) contraindications to MRI (e.g., ferromagnetic implants).

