#### Primary outcome

2.7.2

Derived imaging metrics will be calculated from the acquired rs-fMRI and DTI data as described below. The primary neuroimaging outcomes are defined as the changes from baseline to week 6 in prespecified rs-fMRI metrics (ALFF, ReHo, and FC) and DTI metrics (FA and MD). In addition, 20 healthy controls will undergo baseline rs-fMRI and DTI examinations to provide a reference for PSD-specific neuroimaging alterations.

Rs-fMRI: Rs-fMRI is extensively utilized to probe the neural mechanisms of PSD. The rs-fMRI markers include amplitude of low-frequency fluctuations (ALFF), regional homogeneity (ReHo), and functional connectivity (FC), which can be used to reflect brain function in patients with PSD. However, existing research primarily emphasizes activation in localized brain regions, with insufficient exploration of acupuncture's effect on functional networks in PSD patients (17).

Therefore, we employed rs-fMRI to analyze brain functional network connectivity, aiming to further clarify the central mechanisms underlying acupuncture treatment for PSD.

ALFF: ALFF reflects the local activity level of specific brain regions by calculating signal strength in the 0.01–0.1 Hz frequency band. It is commonly utilized to explore activation patterns in various brain areas, facilitating our understanding of functional changes across different regions following a stroke, particularly those related to swallowing (18).ReHo: ReHo can capture local coherence changes within swallowing-network nodes (e.g., insula, M1, SMA) in PSD by measuring the temporal synchrony between a given brain region and its adjacent voxels, thereby assessing the consistency of neuronal activity within that region (19).FC: Functional connectivity assesses the interconnections between brain regions based on correlations in temporal sequences. Seed-based analysis (e.g., bilateral insula, M1 orofacial area, SMA) and independent component analysis (ICA) employ data-driven methods to capture broader network-level modulation. Evaluating overall connectivity patterns enhances our understanding of how acupuncture may improve neural network function in PSD patients (20, 21).

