### Quality control (QC) & exclusion rules

2.8

Head Motion (rs-fMRI): Frames exhibiting a framewise displacement (FD) greater than 0.5 mm will be scrubbed; datasets with an average FD > 0.2 mm or containing more than 20% high-motion frames will be flagged for exclusion or sensitivity analyses. Summary statistics and outlier count for FD and DVARS will be reported (34, 35).

Image Integrity: Visual quality control will assess co-registration and normalization accuracy, field-of-view coverage, and the presence of artifacts (e.g., ghosting, spikes) (36).

DTI Artifacts: Automatic detection and removal of corrupted directions or slices will be implemented, alongside a review for residual distortion post-TOPUP and EDDY correction (37).

Reproducibility: All parameters, masks, and scripts will be version-controlled (38).

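### The covariate list leaves out time since stroke, and if its covariates enter a two-visit mixed model as main effects only they do not adjust the change contrast in complete pairs

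*Protocol article*

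**What the plan says.** All references are to the Protocol article.

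- **Model (2.11.1, Statistical Modeling).** One model form serves both the clinical and the imaging measures: "linear mixed-effects models will be employed to assess within-subject change (baseline vs. week 6) and between-group differences (acupuncture vs. control"). The covariates stand in the same sentence: "while adjusting for sex, age, stroke severity, and lesion volume". The list has four items. The sentence does not say whether they enter as main effects or with visit interactions, whether the group-by-time term is the test, or whether baseline means are held equal between arms.
- **Primary outcome (2.7.2).** "The primary neuroimaging outcomes are defined as the changes from baseline to week 6 in prespecified rs-fMRI metrics (ALFF, ReHo, and FC"); the DTI measures, FA and MD, are treated the same way.
- **Visits (Figure 3 legend).** "rs-fMRI/DTI at baseline (t0), and Week 6; SSA at t0/Weeks 2/4/6; VFSS/MoCA/SWAL-QOL at t0 and Week 6". Imaging is therefore done twice.
- **Entry window (2.3).** "stroke onset 2 weeks to 6 months prior".
- **Randomization (2.4).** Simple, from a random number table, with no stratification factor named.
- **Size (2.9).** 20 evaluable per group, inflated to 46 in total.
- **Motion (2.8).** At the level of single frames: "Frames exhibiting a framewise displacement (FD) greater than 0.5 mm will be scrubbed". At the level of the whole scan: "datasets with an average FD > 0.2 mm or containing more than 20% high-motion frames will be flagged for exclusion or sensitivity analyses".

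**The concern.** The trial asks whether acupuncture changes brain networks during recovery from stroke. How far a patient is into that recovery at entry bears directly on how much the metrics may change in six weeks without any needle effect. The entry window spans a factor of about 13 (2 to 26 weeks), yet time since stroke is protected neither by stratification nor by the analysis.

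The second problem is less visible. A reader of 2.11.1 would take the primary contrast to be adjusted for four prognostic variables. In the most usual reading of that sentence, the adjustment has no numerical effect on a contrast of changes between two visits. The trial would then report an adjusted result that equals the unadjusted one, with no gain in precision and no correction for imbalance. With about 20 per arm, both matter.

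**Working it through.** **Inputs.** From the article: two imaging visits, two arms, 20 evaluable per arm, 46 randomized 1:1, four covariates, two-sided 0.05, entry at 2 weeks to 6 months. The planned total reproduces as 40 × 1.15 = 46; nothing below turns on it. Assumed: the baseline to week-6 correlation r (shown from 0.3 to 0.9), equal variances at the two visits, the distribution of onset time, and covariates that are fixed per patient (baseline values).

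**1. Why main effects cancel.** For patient i at visit t (0 = baseline, 1 = week 6), arm g and covariates x:

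Y = β0 + β1·g + β2·t + β3·g·t + γ′x + u + e

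The change is D = Y(1) − Y(0) = β2 + β3·g + [e(1) − e(0)]. Both γ′x and the patient effect u drop out. With complete pairs the estimate of β3 is the difference in mean change, whatever x contains. With covariate-by-visit terms δ′x·t, D gains δ′x and the adjustment acts.

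**2. Numerical check.** Two-visit data were simulated with assumed effects (true arm effect 0.5; severity and onset time both influencing change) and fitted by REML with a random intercept, in 100 simulated trials per setting. The table shows how far adding the four listed covariates moved the estimated effect on change.

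| Setting | Shift in the estimate |
|---|---|
| Complete pairs, 20 per arm, main effects | at most 0.00000 (SE moved by at most 0.00001) |
| Complete pairs, covariate-by-visit terms | median 0.098 |
| 6 of 46 week-6 values missing, main effects | median 0.020, maximum 0.076 |
| Complete pairs, baseline means constrained equal, main effects | median 0.038 |

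The standard error was about 0.30 to 0.34. The zero in the first row is algebra and does not depend on the assumed effects; the other rows do. Complete pairs are also what remains under listwise deletion, one of the two options in 2.11.2.

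**3. Precision left unused on baseline.** With unit SD and equal arms, the per-patient variance is 2(1 − r) for change and 1 − r² for ANCOVA. The ratio of ANCOVA to change is (1 − r²) / [2(1 − r)] = (1 + r)/2. The detectable difference at 80% power with 20 per arm is 2.80 × √variance × √(2/20).

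| r (assumed) | ANCOVA / change variance | Detectable, change (SD) | Detectable, ANCOVA (SD) |
|---|---|---|---|
| 0.3 | 0.65 | 1.05 | 0.85 |
| 0.5 | 0.75 | 0.89 | 0.77 |
| 0.7 | 0.85 | 0.69 | 0.63 |
| 0.9 | 0.95 | 0.40 | 0.39 |

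At r = 0.5, ANCOVA on 20 per arm is worth 20/0.75 = 26.7 per arm analysed as change; at r = 0.7, 20/0.85 = 23.5.

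**4. Chance imbalance in onset time.** Assume onset uniform over 2 to 26 weeks: SD = 24/√12 = 6.93 weeks. With 23 per arm, the SE of the difference in means is 6.93 × √(2/23) = 2.04 weeks. A gap above 3 weeks then has probability of about 14%, and above 4 weeks about 5%. Simulating simple randomization of 46, where arm sizes also vary, gave 14.9% and 5.5%.

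**The case against.** The strongest reply is that the article does not say main effects. A condensed protocol commonly leaves model parameterization to the analysis plan, which is not shown and may contain visit interactions or a baseline constraint. This stands, and it is why the cancellation is stated as conditional. It does not reach the covariate list, which the article does fix and which leaves out time since stroke.

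Four stronger readings are tempting, and the documents do not support them.

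- *A reader might infer that the adjustment can never affect the result.* It can, with incomplete pairs analysed by likelihood, under a baseline constraint, or with covariate-by-visit terms.
- *A reader might infer that baseline is ignored.* It is one of the two repeated outcomes in the model. The gap is that neither ANCOVA nor equal baseline means is stated, which is a matter of efficiency and not an error.
- *A reader might infer that head motion is uncontrolled.* Section 2.8 scrubs frames and flags datasets. Motion at week 6 is measured after randomization and may itself change with recovery, so conditioning on it could remove part of a treatment effect.
- *A reader might infer bias.* Under randomization the unadjusted comparison remains valid, and its type I error already allows for chance imbalance.

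It is also fair to say that the article gives no figure linking onset time to change in any metric, so the gain from adding it cannot be computed.

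**Conclusion.** The point holds as a recommended change to the analysis. Two parts rest on the text alone: time since stroke is missing from a stated covariate list despite the wide entry window, unstratified randomization and small arms; and no model form is given in which the listed covariates are certain to act on the primary contrast. If they enter as main effects in an unconstrained two-visit model, the adjustment of that contrast is exactly nil for complete pairs, provided the covariates are fixed per patient.

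The size of the baseline loss depends on r, which the article does not give: ANCOVA variance is 0.75 of change-score variance at r = 0.5 and 0.85 at 0.7, and the advantage nearly vanishes at 0.9. Arm means of onset time more than 3 weeks apart would arise in about 15% of trials if onset were uniform over the window. What is lost is precision and protection against chance imbalance. The randomized comparison is not biased by the omission itself.

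**What to change.** Amend the Statistical Modeling paragraph of 2.11.1, dated before unblinding and before any primary outcome analysis. Section 2.15 reports that at submission the data were blinded and no such analysis had been done. The text should state:

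- For each primary imaging metric, the week-6 value is regressed on arm, the baseline value of the same metric, time since stroke at entry, sex, age, stroke severity and lesion volume, with severity and lesion volume taken at baseline. The arm coefficient is the treatment effect.
- Alternatively, and in effect the same analysis, a mixed model with baseline means constrained equal between arms and covariate-by-visit terms for every covariate, including time since stroke.
- Mean FD at week 6 is added for ALFF, ReHo and FC in a sensitivity analysis only. The scrubbing and flagging in 2.8 stay as they are.

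Cost: wording, plus one or two degrees of freedom. With 40 patients, an intercept, arm and the four listed covariates as single terms leave 40 − 6 = 34 residual degrees of freedom; adding baseline and time since stroke leaves 32. No new measurement is needed: baseline imaging is already planned, and time since onset must be established for eligibility. The baseline items named in 2.4 do not include it, though that list is not exhaustive, so the sponsor should confirm that it is held in the case report form.

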Therefore, in the present study we explicitly separate primary and secondary analyses. The primary (confirmatory) analyses anchor structure-function coupling tests to a prespecified ROI set that captures core swallowing-related hubs with consistent PSD abnormalities (insula, basal ganglia, frontal cortex, M1, SMA, corona radiata, and S1). The secondary (supportive) analyses extend to larger-scale circuits (DMN, frontal–temporal–sensory–motor, sensory–motor–insular–thalamic, and insula–cerebellum–occipital circuits) and are interpreted as hypothesis-generating.

DTI provides complementary insight into the microstructural substrates of PSD. The severity of white-matter injury—reflected by FA and MD metrics—is closely related to the severity of dysphagia, and adaptive white-matter changes may accompany recovery (59). Stroke is associated with disturbances of both functional and structural networks and with state-dependent reductions in functional-structural coupling (60). Therefore, this study included 20 healthy controls as a baseline reference to identify network sites with PSD abnormalities. Combined rs-fMRI and DTI analyses of SC-FC coupling sensitively index clinical impairment and recovery after PSD (46, 60).

Rs-fMRI studies indicate that acupuncture can activate swallowing-related cortical regions in PSD and enhance activity within central swallowing hubs, thereby promoting functional recovery of the cortical swallowing centers. FNIRS evidence suggests that acupuncture facilitates frontotemporal-sensorimotor network integration (61). However, PSD involves not only widespread cortico-cortical injury but also disruption of cortico-subcortical networks, and the mechanisms of structure-function reorganization remain insufficiently understood (51).

Building on this analysis hierarchy, we will examine whether acupuncture-related changes in structure-function coupling and circuit-level functional connectivity track clinical improvement over the 6-week intervention period, using healthy controls as a baseline reference.

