We hypothesize that the Tiao Shen Li Yan acupuncture may improve swallowing function in PSD by enhancing integration within swallowing-related functional networks and promoting microstructural repair of inter-network white-matter pathways, thereby strengthening structure-function coupling across swallowing networks and facilitating functional reorganization of brain networks. In addition to the predefined ROI-based analyses, exploratory whole-brain analyses will also be performed to identify potential PSD-related brain regions that may not be included in the current swallowing network framework. These regions could become targets for future investigations. Importantly, structural and functional connectivity do not necessarily change in parallel during post-stroke recovery. Improvements in functional connectivity in the absence of structural recovery may reflect compensatory reorganization rather than true restoration (62), whereas structural recovery without corresponding functional gains may indicate suboptimal recovery. Therefore, quantifying structure–function coupling may provide mechanistic insight beyond assessing functional or structural metrics alone, by characterizing whether and how functional network reorganization remains constrained by (or diverges from) the underlying structural scaffold.

Overall, a major strength of this study is that it combines rs-fMRI and DTI to establish an “imaging-to-clinic” evidence chain that closely links clinical efficacy with mechanistic evidence. This approach is intended to delineate the structure-function coupling mechanisms by which the Tiao Shen Li Yan acupuncture modulates swallowing networks in PSD, and reveal the mechanism of brain functional network reorganization in PSD patients through acupuncture, while the inclusion of healthy controls enhances clinical relevance and interpretability.

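### The imaging-clinical correlations are specified without arm adjustment or a within-arm restriction, so if the arms are pooled, two separate treatment effects can look like a patient-level link.

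*Protocol article*

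**What the plan says.** The Statistical Modeling paragraph of section 2.11.1 sets out two separate analyses.

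- Linear mixed-effects models cover within-patient change and "between-group differences (acupuncture vs. control), while adjusting for sex, age, stroke severity, and lesion volume". Arm and covariates appear only here.
- The link between imaging and clinical outcome is then tested on its own: "Correlation analyses will test associations between rs-fMRI/DTI metrics and clinical improvement in swallowing function (SSA/VFSS-based measures/MoCA/SWAL-QOL scales". On how, the text says that "analyses will use either Pearson's correlation coefficient or Spearman's rank correlation coefficient", the choice depending on normality and linearity. The stated purpose is modest: "This will aid in assessing whether alterations in brain networks correlate with improvements in swallowing function".

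The Discussion gives the link more weight. There the authors write that "we will examine whether acupuncture-related changes in structure-function coupling and circuit-level functional connectivity track clinical improvement over the 6-week intervention period", and they list as a major strength an "evidence chain that closely links clinical efficacy with mechanistic evidence".

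MoCA stands among the measures of swallowing improvement in the correlation sentence. Section 2.7.3 defines it otherwise: "It will be used to quantify changes in cognitive function attributable to acupuncture".

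**The concern.** A Pearson or Spearman coefficient computed over both arms mixes two sources of covariation: between patients within an arm, and between the two arm means. Only the first bears on whether patients whose brain measures change more also swallow better. The second appears whenever treatment moves both variables, by whatever routes. The trial's own hypothesis in the Introduction is that acupuncture does move both, so the condition for the artefact is the result the authors hope for.

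The mixed models do not repair this, because they test the arm difference in each outcome separately. Changing from Pearson to Spearman does not help either, because ranks carry the arm difference too.

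At stake is the interpretation of the imaging findings. A significant pooled coefficient could be reported as brain change tracking recovery when the data show only two parallel treatment effects.

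**Working it through.** **Inputs from the protocol**
- Evaluable patients: 20 per arm, 40 in total (section 2.9). The plan's inflation reproduces: 40 × 1.15 = 46 randomised, or 23 per arm.
- Allocation 1:1 (section 2.1).
- Two-tailed significance level 0.05 (stated in section 2.11.2).

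**Assumptions**
- Standardised arm effects d1 on imaging change and d2 on clinical change. The article gives neither, so a range is shown.
- Within-arm correlation exactly zero, so that every significant result is a false positive for a patient-level link.
- Both arms pooled, which the text allows but does not state.
- Normal data with unit within-arm variance.

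**Formula.** With 1:1 allocation, the between-arm covariance is d1·d2/4 and the total variances are 1 + d1²/4 and 1 + d2²/4. Hence

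r = (d1·d2/4) / √[(1 + d1²/4)(1 + d2²/4)].

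For d1 = d2 = 0.8 this is 0.16/1.16 = 0.14. For d1 = d2 = 1.0 it is 0.25/1.25 = 0.20.

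**Rejection rates by simulation, 20 per arm** (20,000 trials per setting for equal effects, 40,000 for unequal effects)

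| d1 (imaging) | d2 (clinical) | pooled r | raw Pearson, false positives |
|---|---|---|---|
| 0.5 | 0.5 | 0.06 | 6.8% |
| 0.8 | 0.8 | 0.14 | 13.3% |
| 1.0 | 1.0 | 0.20 | 24.2% |
| 1.2 | 1.2 | 0.27 (simulated mean; formula 0.265) | 39.9% |
| 0.3 | 0.8 | 0.06 | 6.4% |
| 0.5 | 0.8 | 0.09 | 8.5% |
| 0.5 | 1.0 | 0.11 | 10.1% |
| 0 | 0.8 | 0 | 4.9% |

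- Repeat runs with other random seeds agreed within about half a percentage point.
- Raw Spearman is close to Pearson: 6.6%, 13.3%, 24.6% and 41.3% in the four equal-effect rows.
- With 23 per arm, raw Pearson gives 6.6%, 14.6%, 27.1% and 44.9% in those rows. The problem grows slightly with sample size.
- The arm-adjusted (partial) Pearson correlation stays between 4.6% and 5.4% in every setting, so adjusting for arm alone removes the artefact.

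**The case against.** The strongest reply is that the article never says the arms are pooled. The Discussion's reference to acupuncture-related change would fit an analysis within the active arm, where the artefact cannot arise, and a condensed article may leave the analysis population to a fuller document. The first part stands: pooling is a permitted reading, not a stated choice. The second part stands only partly. The article names the estimator and the rule for choosing it, and lists covariates for the neighbouring model but none here. What it does fix has no place for arm.

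A second reply is that the analysis is supportive. That is right. Section 2.9 calls the trial exploratory, and the Discussion makes structure-function coupling in the prespecified regions the confirmatory analysis. The correlations decide nothing about efficacy.

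A third reply is that material inflation needs large effects on both variables. That is also right, as the unequal rows of the table show. Both arms receive the same swallowing rehabilitation, and nothing in the article suggests how large either effect will be.

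A reader might also infer two stronger points that the document does not support.
- One is that time since stroke onset drives both changes. Section 2.3 gives only an eligibility window of 2 weeks to 6 months. No section says how onset time relates to either change.
- The other is that a MoCA correlation would be reported as a swallowing result. Section 2.7.3 and the Discussion both identify MoCA as a cognitive measure, so its place in the correlation sentence is a labelling slip.

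**Conclusion.** The concern holds in a conditional form. The stated method for the imaging-clinical link has no arm adjustment and no within-arm restriction. If both arms are pooled, it cannot separate a patient-level association from two parallel treatment effects.

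Its size depends on the assumed effects. It is negligible if only one variable responds, slight at 0.5 standard deviations on both, and serious from about 0.8 on both, where the false-positive rate is more than twice nominal. The document does not establish that the correlations will be pooled, or that effects of that size will occur. It also does not commit the analysts to an analysis in which the question could not arise.

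**What to change.** State in section 2.11.1 that the association will be estimated as a partial correlation of imaging change with clinical change, adjusted for arm, in Pearson or rank-based form according to the existing rule. This costs one degree of freedom (37 instead of 38 with 40 patients). An equivalent alternative is a regression of clinical change on imaging change with arm and baseline clinical score, which costs one more. Time since stroke onset may be added as a sensitivity covariate. A full interaction model is not needed to remove this defect.

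The adjustment can use masked arm codes, so the analysts stay blinded. It needs only a change of wording, and section 2.15 reports that no primary outcome analysis had been done at submission.

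Two edits to the text go with it. Describe the result as an association, since adjusting for arm does not by itself show mediation, and align the Discussion with that. List the MoCA correlations separately under cognition.
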